### Radiotherapy

Radiotherapy will be conducted as described in Slotman et al [2]. Radiotherapy planning is based on CT no older than 4 weeks (+ 3 days) prior to radiotherapy initiation. In the radiotherapy arm (Arm A), 10 fractions of 3 Gy single dose will be prescribed (total dose 30 Gy). The volume of both normal lungs, i.e. both lungs minus clinical target volume (CTV) receiving more than 20 Gy, is recommended to be kept < 35%. Gross tumor volumes (GTV), comprising the post-chemo−/immunotherapy volume of both the thoracic primary tumor formation and any lymph node metastasis, diagnosed either histologically or by imaging procedures before initiation of medical treatment (chemotherapy, immunotherapy), such as CT, positron emission tomography (PET) /CT or endoscopically assisted ultrasound, (GTV) will be outlined by the responsible clinician. Clinicians are encouraged to design a CTV by adding a safety margin of 6 – 8 mm to the GTV and additionally include hilar, mediastinal and supraclavicular lymph node regions, if these contain lymph node metastases. To design the planning target volume (PTV), additional margins of 6-10 mm axially and 9 – 15 mm in cranial-caudal direction will be added to account for motion and setup errors. Both lungs, esophagus, heart and spinal cord must be outlined throughout the PTV. Both techniques, 3D-conformal and any intensity-modulated photon radiation technique (IMRT, VMAT/Radio ARC), are acceptable. Radiotherapy must be performed with photons at energies ranging from 6 to 23 MeV. Dose prescription will follow international commission of radiation units and measurements reports (ICRU 50, 62, 83).

According to the German S3-guideline (AWMF-Registernummer: 020/007OL), patients can either undergo PCI or imaging controls with 3-monthly MRI examinations and early initiation of radiation in case of subsequent metastases. PCI, if indicated by the treating clinicians, will be conducted according to institutional SOC. Mask fixation, 3D-CT-planning, and photon irradiation with either 5 × 4 Gy, 10 - 12 × 2.5, or 15 × 2 Gy are recommended. Each center has to preselect one prophylactic irradiation scheme for all patients. It is not a requirement to withhold ate-zolizumab during PCI. PCI and thoracic radiotherapy can be performed in parallel.

### Collection of biomaterials for translational research

An accompanying translational research project will investigate the mechanisms behind potential tumor-specific immune effects that might be induced by the combination of ICI and radiotherapy and will explore potential biomarkers for such a treatment. To this end, blood and stool samples will be obtained at baseline, on the first day of the second and the fourth cycle, and at the time of disease progression. Collection of tumor tissue samples will take place at baseline and is highly recommended in case of a re-biopsy after disease progression under study treatment. While the baseline tissue collection is mandatory, collection of all other biomarker samples is optional, i.e. patients can participate in the clinical trial if they do not consent to the collection of biomarker samples.

### Study endpoints

The primary endpoint of the TREASURE trial is OS defined as time from randomization to death due to any cause. Secondary efficacy endpoints include 1- and 2-year OS rates, PFS, response rate, and the intrathoracic tumor control defined as rate of intrathoracic progression and time to intrathoracic progression. Moreover, safety will be assessed by evaluating the incidence, nature, causal relationship and severity of adverse events according to CTCAE v5.0 (with special focus on pulmonary events including pneumonitis; hepatic, gastrointestinal, endocrine, ocular, dermatologic, renal and pancreatic events including pancreatitis; immune-mediated myocarditis and myositis as well as infusion-related reactions and cytokine-release syndrome) and the frequency of abnormal laboratory parameters, and feasibility will be addressed in terms of frequency of treatment withdrawal, i.e. due to adverse events or other reasons, and completion of radiotherapy. Furthermore, cancer-related quality of life will be measured using the Functional Assessment of Cancer Therapy – Lung (FACT-L) questionnaire. The planned biomarker analysis of biomaterials that will be collected during the clinical trial is an exploratory endpoint of the TREASURE study.

### Statistical analysis

Statistical analysis is in accordance with the International Conference on Harmonization (ICH) Guidelines “Structure and Content of Clinical Study Reports” and “Statistical Principles for Clinical Trials”. All statistical analyses will be done according to the current SOPs of the Institute of Medical Biometry and Informatics (IMBI), University of Heidelberg, using SAS version 9.4 or higher.

#### Sample size calculation

With *n =* 104 patients, under the assumption of a 20% improvement (from 52 to 72%) in the 12-month OS rate, a difference between treatment groups with regard to the primary endpoint OS can be detected with a power of 80% using a log-rank test at a two-sided alpha of 5%, assuming a dropout rate of about 10%, follow-up phase of 24 months, and an accrual period of 24 months. This improvement of 20% points corresponds to the effect of the radiation therapy together with the one mediated by ICI [2, 6]. Based on these assumptions, the resulting total sample size yielding the necessary number of 66 events is 92 patients (46 per arm) to achieve a power of 80%. In order to adjust for dropouts, *n =* 104 patients have to be randomized.

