One approach that has been explored in the past is the addition of thoracic radiotherapy (TRT) to chemotherapy. In a phase III randomized trial, Slotman et al demonstrated an increased 2-year survival rate with low toxicity rates for patients who received TRT (30 Gray [Gy] in 10 fractions) in addition to prophylactic cranial irradiation (PCI) after any response towards standard chemotherapy, compared to patients who did not receive TRT [2]. Progression was less likely in the TRT group (hazard ratio [HR] = 0.73, *p* = 0.001) with an almost 50% reduction in intrathoracic recurrences. The randomized phase II RTOG-0937 trial was designed to evaluate PCI ± consolidative RT to intrathoracic disease and limited extracranial metastases in ED-SCLC patients. Results of RTOG-0937 showed that consolidative RT prolonged progression free survival (PFS), but did not improve 1-year overall survival (OS) [3]. Since both studies provide interesting signals for a potential benefit of local thoracic consolidation, but failed to reach statistical significance within their trial designs, a controversial discussion about who might profit from thoracic radiotherapy is ongoing. Based on German guidelines (Onkopedia and consultation version of new S3-guideline), thoracic radiation can be offered to patients with residual disease following systemic treatment on an individual basis. This is in line with the ESMO guidelines, which mention consolidation radiotherapy to the residual tumor and lymph nodes as a treatment option (grade C, level II recommendation) for patients with a performance score of 0-2 who achieve a response after chemotherapy, while the ASTRO guidelines strongly recommend thoracic radiotherapy for patients with a response to chemotherapy alone but residual tumor in the thorax. At the same time, all guidelines stress that there is a lack of data considering the implementation of consolidation thoracic radiotherapy to immunochemotherapy in ED-SCLC. The advent of immunotherapies has revolutionized the management of several tumor entities, including advanced non-small cell lung cancer (NSCLC). Here, upfront mono- or combination therapies with immune checkpoint inhibitors (ICI) are now standard of care in the majority of patients. Considering their high mutational burden, SCLC tumors were also expected to respond well to this type of treatment. Indeed, results from several clinical trials suggest that SCLC patients may benefit from such therapies [4, 5]. In particular, the addition of a programmed death-ligand 1 (PD-L1) checkpoint inhibitor to chemotherapy in order to enhance T cell-mediated immunity appears to be very promising, as was demonstrated by the results of the IMpower133 trial [6]. Here, adding the PD-L1 antibody atezolizumab to carboplatin/etoposide induction therapy followed by an atezolizumab maintenance therapy significantly prolonged OS and PFS compared to the placebo arm. Results of the CASPIAN phase 3 study, where combination of platinum-etoposide with durvalumab in first-line treatment for patients with ED-SCLC resulted in stable and persistent clinical benefit across OS, PFS, and objective response [7], align with Impower133 trial findings. Addition of pembrolizumab (anti-PD-1) to etoposide and platinum treatment, as part of the KEYNOTE 604 study, significantly prolonged PFS in comparison with placebo plus etoposide and platinum as first-line therapy for patients with ED-SCLC [8]. Despite these encouraging data on outcome, the question remains how the response can be further increased.

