**Fig. 1 Fig1:**
[figure not shown]
TREASURE study design. ED SCLC patients with any response (defined as CR/PR or thoracic SD with CR/PR of extrathoracic lesions) after four cycles of standard chemo-immunotherapy consisting of carboplatin/etoposide and atezolizumab will be randomized to either receive thoracic radiotherapy or not. All patients will receive maintenance atezolizumab therapy until disease progression or occurrence of intolerable toxicities

**Table 1 Tab1:** Key inclusion and exclusion criteria of the TREASURE trial

Inclusion criteria	Exclusion criteria

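### The 20-point survival gain behind the 80% power includes an immunotherapy effect that both arms receive, so its stated basis does not support HR 0.50 for thoracic radiotherapy added to atezolizumab

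*Protocol article*

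**What the plan says.** The sample size section of the protocol article plans the trial "under the assumption of a 20% improvement (from 52 to 72%) in the 12-month OS rate", "with a power of 80% using a log-rank test at a two-sided alpha of 5"%, and states that "the resulting total sample size yielding the necessary number of 66 events is 92 patients (46 per arm) to achieve a power of 80"%. Its timing inputs are given as "assuming a dropout rate of about 10%, follow-up phase of 24 months, and an accrual period of 24 months". Allowing for dropout brings the number randomised to 104.

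The next step is the reason given for the 20 points: "This improvement of 20% points corresponds to the effect of the radiation therapy together with the one mediated by ICI [2, 6"]. The Background describes both references. Reference 2 randomised patients to TRT or no TRT after a response to standard chemotherapy. Reference 6 added atezolizumab or placebo to carboplatin/etoposide.

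The design itself separates the arms only by TRT. The study design section requires four induction cycles that include atezolizumab before entry and gives the main objective as the gain from adding TRT. The Fig. 1 caption says: "All patients will receive maintenance atezolizumab therapy until disease progression or occurrence of intolerable toxicities". Under Study procedures, arm B receives atezolizumab at the same dose and interval as arm A.

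**The concern.** The planned difference is a difference between arms. A component that both arms receive adds nothing to it. The sum of a TRT effect (from reference 2) and an atezolizumab effect (from reference 6) describes patients given both treatments compared with patients given neither, and this trial has no such comparison.

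The article gives no source for the 52% control rate, and neither obvious origin rescues the sum. If 52% already reflects chemo-immunotherapy, the immunotherapy effect is counted twice. If it reflects chemotherapy alone, it is not the expected rate in arm B.

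At stake is what the 80% means. A reader will take it as the power to detect the effect that the literature suggests for TRT on top of atezolizumab. The article supplies no such effect. Of the second randomised radiotherapy trial, the Background says that it "did not improve 1-year overall survival (OS) [3"]. Of both radiotherapy trials, it says that they give interesting signals "but failed to reach statistical significance within their trial designs". It adds that data on TRT combined with immunochemotherapy are lacking.

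**Working it through.** **Inputs.** From the sample size section: 12-month survival 52% and 72%, two-sided alpha 5%, power 80%, 66 events, 92 evaluable patients, 24 months of accrual, 24 months of follow-up, dropout about 10%. From Study procedures: 1:1 allocation. Assumed for the check: exponential survival and uniform accrual.

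**Step 1: reproduce the plan's figures.**

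- HR = ln(0.72)/ln(0.52) = 0.502.
- Events (Schoenfeld) = 4 × (1.960 + 0.842)² / (ln 0.502)² = 66.2. The article states 66.
- Power at 66 events = Φ(|ln 0.502| × √66/2 − 1.96) = 0.799.
- Event probability by the end of the study, with accrual A = 24, follow-up F = 24 and λ = −ln(S₁₂)/12, is 1 − [exp(−λF) − exp(−λ(A+F))]/(λA). This is 0.849 at 52% and 0.620 at 72%, mean 0.735.
- Patients = 67/0.735 = 91.2 (66.2 rounded up to 67 whole events), or 92 in equal arms.
- Dropout: 92/0.90 = 102.2, so 103, or 104 in equal arms.

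The calculation is therefore correct for its inputs. Only the reason given for the effect size is in question.

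**Step 2: compare the contrasts.**

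| Comparison | TRT differs | Atezolizumab differs |
|---|---|---|
| Reference 2, as the Background describes it | yes | no (chemotherapy only) |
| Reference 6, as the Background describes it | no | yes |
| Sum used for the 20 points | yes | yes |
| Arm A against arm B | yes | no |

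The last two rows do not match. Neither reference, as described, measures an interaction between the two treatments.

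**Step 3: how power depends on the TRT share.** The article does not split the 20 points, so the TRT-only gain below is an assumption, with control held at 52%. Power is Φ(|ln HR| × √d/2 − 1.96), first with d = 66 and then with d = the deaths expected among 92 patients from the formula in step 1. The second version is needed because the article gives accrual and follow-up periods and does not say that the analysis waits for exactly 66 events; a weaker effect yields more deaths.

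| Assumed TRT-only gain | HR | Power, 66 events | Expected deaths in 92 | Power at those deaths |
|---|---|---|---|---|
| 20 points | 0.502 | 80% | 67.6 | 81% |
| 18 points | 0.545 | 69% | 68.9 | 71% |
| 15 points | 0.612 | 51% | 70.9 | 54% |
| 10 points | 0.731 | 25% | 73.7 | 27% |
| 5 points | 0.860 | 9% | 76.1 | 10% |

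**Step 4: power at 66 events for round hazard ratios.** With √66/2 = 4.062: HR 0.50 gives Φ(2.816 − 1.96) = 80%; 0.60 gives Φ(2.075 − 1.96) = 55%; 0.70 gives Φ(1.449 − 1.96) = 30%; 0.75 gives Φ(1.169 − 1.96) = 21%.

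**The case against.** The best defence is synergy. The Abstract and Background argue that radiotherapy can trigger an immune response that checkpoint inhibition then amplifies. A gain of that kind would arise only in arm A and would not cancel, and the sentence could be read as meaning it. This stands as a possible assumption, but not as what is written: the sentence names two effects and supports them with two separate main-effect comparisons. If synergy is meant, it has to be stated, and references 2 and 6 cannot carry it.

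A second defence is that the power statement is conditional. It says what the trial can detect if survival rises from 52% to 72%, and that is true of arm A against arm B. This also stands. A reader might infer that the 80% is wrong or does not apply to the randomised contrast; it is right for HR 0.50. An ambitious target is also legitimate in phase II, provided it is presented as a target.

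A third defence is that the evidence on TRT is mixed rather than negative. The Background also credits reference 2 with better 2-year survival, and a time-to-event analysis is not confined to the first year. This is fair. The Background passages show that the article offers no support for a 20-point TRT effect; they do not show that TRT has none.

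**Conclusion.** The point holds as a fault in the stated basis of the effect size. An immunotherapy main effect is present in both arms and cannot contribute to the TRT contrast. At 66 events any positive immunotherapy share of the 20 points takes power below 80%; a share of only 2 points would already bring it to about 69–71%.

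How much power is lost cannot be determined from the article, because the 20 points are not divided and the 52% has no source. The figures of 51–54%, 25–27% and 9–10% are illustrations that rest on an assumed TRT gain, exponential survival and a 52% control rate.

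Two stronger readings are tempting. One is that the true power is about 25%, because 10 points corresponds to HR 0.73 and the Background quotes a hazard ratio of 0.73 for TRT. That figure is for progression, not survival, so it does not anchor the row. The other is that a non-significant result is likely even if TRT works, and would be taken as no benefit. The first part depends on the unknown TRT effect, and nothing in the article says that a null result would be read that way.

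**What to change.** In the sample size section, remove the clause that adds the immunotherapy effect to the radiotherapy effect. Then do one of two things:

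1. State the effect expected from TRT added to atezolizumab, or state a TRT–immunotherapy synergy assumption in so many words without attributing it to references 2 and 6, and restate the power for that effect.
2. Keep HR 0.50 and call it a detectable difference, not an effect that references 2 and 6 support.

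In either case, report power at 66 events for HR 0.50, 0.60, 0.70 and 0.75: about 80%, 55%, 30% and 21%. Keep 104 patients, the endpoint and the test.

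The work is a rewording and one short table. The price is a less favourable stated power for effects smaller than HR 0.50; no further patients are needed.

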#### Interim safety analysis

A safety interim analysis will be performed in Arm A after *n =* 23 patients in this arm have been followed for 12 weeks after the end of thoracic radiotherapy. With a sample size of *n =* 23, it will be possible to distinguish between two scenarios for the safety variable:

1. a toxicity scenario, where the grade ≥ 3 pneumonitis rate is assumed to be pTox = 0.125 (based on NICOLAS trial [18] and own unpublished data).

2. a non-toxicity scenario, where the grade ≥ 3 pneumonitis rate is assumed to be pTox = 0.02 (based on IMPower133 [5] and data from trials with other programmed death-1 [PD-1]/PD-L1 inhibitors [19–22]).

If among 23 patients the number of patients with a grade ≥ 3 pneumonitis (X) is 2 or more, no further patients will be recruited to the trial.

Under the above assumptions, the probability to correctly detect the toxicity scenario amounts to P [X ≥ 2|pTOX = 0.125] = 0.801, while the probability to correctly continue amounts to P [X ≤ 1|pTOX = 0.02] = 0.923, assuming binomially distributed variables. Assuming that both scenarios are equally likely, this will yield an overall correct decision probability of 0.862.

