**Methods/design:**

The TREASURE trial is a randomized, multicenter, phase II clinical trial (ClinicalTrials.gov identifier, NCT04462276). One hundred four patients suffering from extensive disease (ED) SCLC, with any response to the standard of care induction chemo-immunotherapy will be randomized to receive atezolizumab maintenance therapy with or without TRT. The primary endpoint of this study is overall survival (OS). Secondary endpoints include further measures of efficacy, safety, and the collection of biomarker samples. A safety interim analysis will take place after *n* = 23 patients receiving TRT have been observed for three months after the end of TRT.

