### Study procedures

Before a patient’s involvement in the clinical study, the investigator is under obligation to obtain written informed consent. The randomization will be done by a validated program using variance minimization method [17]. All randomization design aspects and patient allocation statuses underly strict access control. The allocation of the patient numbers and treatment groups will be coordinated by an Interactive Web Response System (IWRS) system integrated in the eCRF. After 1:1 randomization, eligible patients will receive either atezolizumab (1200 mg fixed dose, every 3 weeks [Q3W]) and TRT (30 Gy in 10 fractions) in arm A or atezolizumab only (1200 mg fixed dose, Q3W) in arm B. Patients will be stratified during randomization according to presence of brain metastases (yes vs no), thoracic response after induction therapy (complete/partial response [CR/ PR] vs stable disease [SD]), and prophylactic cranial irradiation PCI (yes vs no). Treatment will be discontinued in case of progressive disease, unacceptable toxicity, on patients’ request, or at the end of study.

In order to ensure patient safety with regard to a potential increase in risk of treatment-related pneumonitis when combining TRT with immune checkpoint inhibition, a safety interim analysis will be performed in arm A after *n =* 23 patients have been followed for 3 months after the end of TRT. If in this cohort the number of patients with a grade ≥ 3 pneumonitis is 2 or more, recruitment to the trial will be stopped. All evaluations will be performed by the medically responsible experts of this trial, i.e. the Coordinating Investigator, the Deputy Coordinating Investigator and the Mentoring Coordinating Investigator– under support of the study statistician as far as applicable. They will provide their opinion to the Sponsor or its delegate who will be responsible for the formal decision on termination / continuation. The Safety Monitoring Committee (SMC) will additionally review all evaluations / decisions and provide its opinion to the Sponsor.

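### The pneumonitis stopping rule is read once, when 23 irradiated patients have completed follow-up, although a second grade ≥ 3 case already settles it; reading it at the second case would spare TRT exposure at no cost in error rates

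*Protocol article*

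**What the plan says.** Three places in the protocol article describe the rule, and all three tie it to completed follow-up.

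- Abstract, Methods/design: the interim takes place after 23 "patients receiving TRT have been observed for three months after the end of TRT".
- Study procedures: it takes place in arm A after 23 "patients have been followed for 3 months after the end of TRT"; if the number with grade ≥ 3 pneumonitis "is 2 or more, recruitment to the trial will be stopped".
- Interim safety analysis: it takes place after 23 "patients in this arm have been followed for 12 weeks after the end of thoracic radiotherapy", and "If among 23 patients the number of patients with a grade ≥ 3 pneumonitis (X) is 2 or more, no further patients" will enter the trial.

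Interim safety analysis sets the rule between two scenarios: in one the "rate is assumed to be pTox = 0.125", in the other the "rate is assumed to be pTox = 0.02". The first gives "P [X ≥ 2|pTOX = 0.125] = 0.801"; the chance of correctly continuing under the second is given as 0.923, and the average of the two as 0.862.

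Study procedures adds that the coordinating investigators evaluate the data, the sponsor takes the formal decision, and the Safety Monitoring Committee (SMC) reviews evaluations and decisions. The article mentions neither a review prompted by an individual event nor a pause in accrual while the 23 are followed.

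**The concern.** The trigger is the calendar (23 patients with complete follow-up), but the decision depends only on whether the count reaches 2. Once two patients in the cohort have had grade ≥ 3 pneumonitis, no later observation can turn the result into a decision to continue. Waiting for the rest of the cohort adds nothing to this decision.

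Study procedures says the look exists because TRT combined with checkpoint inhibition may raise the risk of pneumonitis. If nothing outside the article intervenes, patients could still be randomized to TRT after the rule's own criterion has been met. That would happen in exactly the scenario the rule was built to detect.

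**Working it through.** **1. The printed operating characteristics.** Inputs from Interim safety analysis: n = 23, boundary X ≥ 2, rates 0.125 and 0.02.

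- P(X ≥ 2 | 0.125) = 1 − 0.875^23 − 23 × 0.125 × 0.875^22 = 1 − 0.0464 − 0.1523 = 0.8013 (printed 0.801).
- P(X ≤ 1 | 0.02) = 0.98^23 + 23 × 0.02 × 0.98^22 = 0.6283 + 0.2949 = 0.9233 (printed 0.923).
- Mean = (0.8013 + 0.9233)/2 = 0.8623 (printed 0.862).

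All three reproduce.

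**2. The same boundary read at the second case.** The second case falls in the k-th cohort patient with probability (k − 1) p² (1 − p)^(k−2). Summed over k = 2 to 23, this gives 0.8013 at p = 0.125 and 0.0767 at p = 0.02, so the chance of continuing in the second scenario is 1 − 0.0767 = 0.9233. These are the values in step 1: the same trials stop, only sooner. At p = 0.125, given a stop, the second case is on average in patient 11.8 of 23 (median 11).

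**3. When the scheduled look falls.** Inputs from the article: 104 patients in 24 months (Study design section), 1:1 allocation (Study procedures), TRT over 2 weeks (Table 2, footnote f), 12 weeks of follow-up. Assumed: even accrual and TRT starting 7 days after randomization.

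- Arm A accrual: 104/24/2 = 2.167 per month.
- Look: 23/2.167 + (7 + 14 + 84)/30.44 = 10.6 + 3.4 = about month 14, with about 30 arm A patients randomized.
- Slower accrual: the Study design section also gives recruitment from September 2020 to July 2024, about 46 months. Then 104/46/2 = 1.130 per month, and the look is at 23/1.130 + 3.4 = about month 24, with 26 to 27 arm A patients.

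**4. Time from second case to look, by simulation.** p = 0.125, given a stop. The article gives no onset timing, so two assumptions were run: onset uniform over the 12 weeks, and every case at the end of week 12. The second gives the shortest delay.

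| Accrual | Onset | Mean delay (months) | Further arm A patients | Delay over 1 month |
|---|---|---|---|---|
| 24 months | uniform | 6.5 | 14 | 98% |
| 24 months | all at week 12 | 5.2 | 11 | 91% |
| 46 months | uniform | 11.3 | 12 | 99% |
| 46 months | all at week 12 | 9.8 | 11 | 95% |

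Repeating the runs with random (Poisson) arrivals and with a 14-day lag to TRT changed these results little.

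**5. Without conditioning on a stop.** Averaged over the whole 12.5% scenario, the further patients number about 0.801 × 11 = 9 to 0.801 × 14 = 11.

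**The case against.** The strongest objection is that silence is not prohibition. A reader might infer that nothing happens until the cohort matures and that accrual definitely runs on. The article does not say so. It says when the formal look is made and which count stops recruitment. Adverse events are assessed continuously, an SMC exists, and the sponsor can decide on termination. Event-driven review and accrual holds commonly sit in the full protocol or SMC charter, which are not shown. This stands: the months and patient numbers hold only if those documents do not act earlier. It does not remove the point, because the article states the rule's timing three times, always as completed follow-up.

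A second objection is that the second case settles the matter only if both patients belong to the 23. The Abstract counts patients who received TRT, and Interim safety analysis counts patients followed for 12 weeks. Whether a patient who dies or drops out before week 12 counts or is replaced is not stated. Reading the rule early in the first 23 patients randomized to arm A would therefore not match the printed cohort. This also stands, and any change needs a cohort definition.

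Third, a single-look binomial rule is a recognized phase II design, and its printed error rates are right. That is true, and it limits the rating: this is an improvement, not the correction of a wrong figure.

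**Conclusion.** The point holds in conditional form. As printed, the rule is read once at completed follow-up, with no stated earlier trigger or accrual hold, although a second grade ≥ 3 case in the cohort already decides it.

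Unless an unseen document acts earlier, at a 12.5% rate and given a stop, the mean delay is about 5 to 6.5 months at the planned accrual and about 10 to 11 months at 46-month accrual. About 11 to 14 more patients are randomized to arm A meanwhile. The delay is not always long: it is under one month in about 2 to 9% of stops at the planned accrual, when the second case falls late in the cohort. The ranges rest on the assumed onset timing, accrual pattern and lag to TRT.

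A reader might go further and conclude that the rule's probabilities are wrong or that patients will certainly be exposed after the criterion is met. The documents support neither.

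**What to change.** Keep n = 23 and the threshold of 2, and change only when the rule is read:

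- Define the cohort prospectively as the first 23 arm A patients who start TRT, and state one way of counting those who die or drop out before week 12.
- Apply the existing recruitment stop when the second grade ≥ 3 pneumonitis within the 12-week window is confirmed in that cohort. The Abstract and Study procedures say three months, so all three places should give the same window.
- Keep the look at 23 completed patients as the point at which a decision to continue is made.
- If the full protocol or SMC charter already provides an earlier trigger, refer to it beside the rule.

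The cost is a short amendment to the protocol and SMC charter, and the work of confirming and counting pneumonitis cases as they are reported. Sample size does not change, and for the same cohort 0.801, 0.923 and 0.862 stay as printed.
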